The primary outcome of this study is to determine if individualised OHI combined with DOHE improves approximal plaque index (API) (81) scores between baseline and the 6-week follow-up, compared with usual care/no OHI education. Secondary outcomes of this study will determine if digitally delivered oral health education alone or partnered with individualised OHI improves API scores between baseline and the 12-week follow-up, compared with usual care. It will compare the mean reduction of API and SBI between each group at baseline and follow up, and determine if any participant reaches scores that are clinically significant. It will assess any changes to patients’: motivation, confidence, and behaviour regarding their oral hygiene practices, knowledge of oral health impacts on cardiovascular health, as well as their experience with oral care whilst on the ward. Additionally, it will assess the cardiac nursing staff views on an oral health education program within the rehabilitation facility. As good oral hygiene habits are an upstream approach of reducing risk of systemic chronic inflammation, and as such, risk of a future cardiac event (29), we hypothesise introducing an individual OHI partnered with DOHE program into the cardiac rehabilitation out-patient clinic will help improve API scores between baseline and follow-up. We also hypothesise the program will increase patients’ awareness of the impact of oral health on cardiovascular health and help to motivate and give them confidence in caring for their oral health; and if not doing so already, incorporating regular visits to an OHP.

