- Assess the percentage in each Group that has reached clinically significant SBI scores of ≤25%.
- Assess the percentage in each Group that has reached clinically significant API scores of ≤35% as well as a clinically significant SBI scores of ≤25%.
- Improved oral hygiene habits as reported by an increase in brushing frequency and/or inclusion of interproximal cleaning, comparing baseline to follow-up.
- Improved understanding between the link between heart health and oral health (Likert scale). A yes response increase of ≥ 5 out of 12 will be considered as an improved understanding.
- Confidence to improve oral hygiene habits with a self-reported 5-point Likert scale. A change in response from neutral, disagree or strongly disagree to agree or strongly agree compared to baseline will be considered confident.
- Motivation to improve their oral health and see an OHP regularly with a yes/no response and a self-reported 5-point Likert scale. Answer change from no to yes will be considered motivated to improve their oral health and a response of: ‘Yes I have made an appointment since the assessment’ or ‘Yes, however I have not yet made an appointment’ will be considered motivated to visit an OHP regularly.
- Patient perceptions of a nurse’s role in their oral health care using yes, no answers. Answering yes will be considered cardiac nurses can play a role in their oral health.
- Cardiac nurse perception of the importance and effectiveness of the intervention in the rehab setting (Likert scale). A response of 4 or 5 will be considered as the intervention being important and effective.

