**Data collection and management**

Data will be collected at baseline, 6 weeks and at the final 12-week assessment and stored via REDCap. Baseline data will include demographic information, medical history, weight (kg), height (cm), body-mass index (BMI), oral hygiene practices, and oral hygiene knowledge associated with CVD. CEAP nurses record weight, height, and BMI when patients first attend the program, as such this data and other required medical data will be retrieved from participant clinical records. Questionnaires delivered via REDCap via iPads. Clinical parameters will be recorded at baseline, the 6-week, and the final follow-up after 12 weeks. PSR, SBI, and API will be completed using a disposable World Health Organisation (WHO) periodontal probe and mirror, with tricolour disclosing gel. For timeline and mode of collection see **Table 1**.

Each site will hold a master spreadsheet held on WSLHD servers. Identifiable data including name, address and phone numbers will be housed on secure servers within the WSLHD network. The server is managed and maintained by WSLHD Digital Health Services (DHS). Each patient will be assigned a code – the patient’s name and dental record number will be linked to the study code and stored in an encrypted and password protected folder, separate to all other data files, with access to this folder limited to the principal investigator and coordinating principal investigator. All other data files will contain only the study code. Participant consent forms will be in digital form as part of REDCap, thus stored electronically. Data sheets will contain the study code, age and sex and will be stored electronically. De-identified data will be used for any analyses and publications and all data collected during the study will be retained for a period of 5 years following the study completion. We anticipate no harm resulting from the intervention, as such we do not require a data safety monitoring board.

**Table 1.** Timing and mode of collection of study data

| Measurements and Surveys | Baseline | 6-week  Assessment | 12-week  Final Assessment |
| --- | --- | --- | --- |
| Demographic information and medical history and behaviour/risk factors | X |  |  |
| Clinical measurements PSR/API/SBI | X | X | X |
| Oral health Perceptions and knowledge | X | X | X |
| Oral hygiene habits | X | X | X |
| Motivation and confidence and to improve oral hygiene practices | X | X | X |

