**Sample size**

The required sample size for this study is calculated to be a total of 165 (1:1:1 Group A: Group B: Group C). This calculation includes provision for a 10% attrition rate, two tailed tests, type 1 error of 5%, and will have 80% power to detect any significant difference between Group A and Group C. This calculation is based from an API score reduction of 25% in the intervention arm of Ziebolz, et al 2009 study (87). However, due to our exclusion criteria of ≤59% API score, we will expect to see a 40% decrease in Group A, compared to 15% in Group C. This current study is powered to detect a difference in percentage proportion of those between Group A and Group C however, has poor power to detect a difference between Group B and Group C.

| Table 2. Adapted API/SBI measurement results (88) | | |
| --- | --- | --- |
|  | **API** | **SBI** |
| Poor oral hygiene | >35% | >25% |
| Fair oral hygiene | 35% | 15-25% |
| Good oral hygiene | <25% | <15% |

| Table 3. Adapted PSR code definitions (86,89). | |
| --- | --- |
| Code | Clinical Signs |
| 0 | Absence of clinical signs: no calculus, or BOP  Coloured band on WHO probe completely visible. |
| 1 | No calculus.  BOP  Coloured band on WHO probe completely visible. |
| 2 | Supra and/or subgingival calculus  BOP  Coloured band on WHO probe completely visible. |
| 3 | Periodontal pocket 3.5mm-5.5mm  Coloured band on WHO probe partially visible |
| 4 | Periodontal pocket >5.5mm deep  Coloured band on WHO probe no longer visible |
| X | Sextant absent of dentition |
| * | Periodontal abnormalities which include:  Furcation involvement  Mobility  Mucogingival problems for example: exudate, severe oedema  >3.5mm recession  The * is recorded next to the sextant number code. E.g. “3*” |

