**Statistical analysis**

The statistical plan for this study will be determined prior to study completion. Analysis of the difference in API will be according to the intention-to-treat principle where participants are analysed in the arm they have been allocated. The level of statistical significance will be set at p-value <0.05. The primary analysis will be an adjusted analysis of variance performed to assess differences between groups for API scores between baseline and follow-up. Covariates used for adjusted analyses will include age, sex, highest PSR code, level of education, smoking status, and number of teeth. Subgroup analysis of the intervention effect and age, sex, education, ethnicity, and cardiovascular disease presentation (coronary heart disease, heart failure, heart transplant list, heart transplant receiver) will also be explored. Outcome measures available at baseline (PSR, SBI and API) will also be included in the statistical model. An unadjusted analysis will be performed to assess differences between groups using a X^2^ test for binary (categorical) outcomes and independent sample t-tests for continuous outcomes.

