**Conclusion**

The link between oral health and CVD has been proven (18,21,29). For the average patient with CVD, the accessibility of information regarding the importance of this link and the impacts oral hygiene practices has on their cardiovascular health, are almost non-existent (28,45–49). As such, oral health knowledge and the importance of oral hygiene amongst this population is minimal (74). Digital educational programs have proved effective in increasing knowledge, confidence, and motivation to improve health outcomes (77), even when literacy levels are low (78,79). Therefore, this study will assess if the introduction of individualised OHI and a DOHE instrument will influence the API score, oral health, practices, knowledge, and motivation of CVD patients attending a cardiac rehab out-patient facility.

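### The rule for improved understanding (a rise of at least 5 out of 12) cannot class anyone with a baseline of 8 or more as improved and ignores every gain of up to 4, so this secondary outcome loses power

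*Protocol*

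**What the plan says.** In the introduction, at the end of Oral health promotion studies, the protocol states a hypothesis about awareness: "We also hypothesise the program will increase patients’ awareness of the impact of oral health on cardiovascular health". The matching secondary outcome under Study outcomes begins "Improved understanding between the link between heart health and oral health (Likert scale") and is then defined by a single rule: "A yes response increase of ≥ 5 out of 12 will be considered as an improved understanding". The label names a Likert scale; the rule counts 'yes' answers.

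No baseline limit, restricted denominator or category for participants who already score high goes with the rule. For API and SBI the same list includes between-group comparisons of mean reduction. For understanding it lists only the flag.

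Statistical analysis assigns the test for such a flag: "An unadjusted analysis will be performed to assess differences between groups using a X^2^ test for binary (categorical) outcomes". Table 1 has knowledge collected at baseline, 6 weeks and 12 weeks. Participant eligibility contains no criterion on knowledge. The only indication of the expected baseline is qualitative and stands in the Conclusion: "oral health knowledge and the importance of oral hygiene amongst this population is minimal".

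**The concern.** A fixed absolute gain on a bounded scale has two consequences. Participants near the top have no room to reach the threshold and are counted as failures whatever they learn. Participants lower down who learn something, for example moving from 3 to 7, are counted the same as those who learned nothing.

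At stake is the one listed outcome that tests the awareness hypothesis between arms. If many participants start high, or the videos teach a few items rather than many, the percentage improved is held down in every arm and the A–C and B–C contrasts shrink. The trial could then report no difference in understanding although the package works. The protocol fixes this threshold itself, so this is not a detail left for the statistical analysis plan.

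**Working it through.** **1. The plan's own figure.** The protocol gives no power for understanding; its calculation is for the primary outcome (Sample size: "This calculation includes provision for a 10% attrition rate, two tailed tests, type 1 error of 5%, and will have 80% power"; "we will expect to see a 40% decrease in Group A, compared to 15% in Group C"). Reading 40% and 15% as proportions of responders:

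n per arm = [1.96·√(2 × 0.275 × 0.725) + 0.8416·√(0.40 × 0.60 + 0.15 × 0.85)]² / 0.25² = (1.238 + 0.510)² / 0.0625 ≈ 48.9, so 49.

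49 / 0.90 = 54.4, so 55 per arm, and 3 × 55 = 165. The stated total is reproduced. The figure of 49 evaluable per arm is used below.

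**2. The ceiling.** Largest possible gain = 12 − baseline. The rule needs 12 − baseline ≥ 5, that is, a baseline of 7 or less.

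| Baseline | 7 | 8 | 9 | 10 | 11 | 12 |
|---|---|---|---|---|---|---|
| Largest gain | 5 | 4 | 3 | 2 | 1 | 0 |
| Can be classed as improved | yes | no | no | no | no | no |

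Five of the 13 possible baseline scores can never qualify.

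**3. The cut-off.** At baselines of 0–7 a gain of 1–4 is also scored as no improvement. If unknown items are learned with probability 0.45, 5% of known items are lost and the baseline mean is 2.4, the mean gain is 0.45 × 9.6 − 0.05 × 2.4 = 4.2 items, which is below the threshold. With 0.25 it is 0.25 × 9.6 − 0.12 = 2.28.

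**4. Power under assumed models.** The protocol gives no baseline distribution and no learning rate, so everything here is an assumption: 49 per arm, two-sided 5%, beta-binomial baseline with precision 6, 5% of known items lost. The flag is compared by X²; the count is compared with the baseline count as covariate.

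Large effect (unknown items learned with probability 0.45 in Group A, 0.25 in Group C):

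| Baseline mean (of 12) | At 8 or more | Power, flag | Power, count |
|---|---|---|---|
| 2.4 | 3% | 99% | over 99% |
| 3.6 | about 8.5% | 96% | over 99% |
| 4.8 | 18% | about 86% | over 99% |
| 6.0 | 31% | about 69% | 99% |
| 7.2 | 48% | about 42% | 97% |
| 8.4 | 67% | about 11% | 88% |

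Smaller effect (0.35 against 0.25), at the low baselines that fit the protocol's own description:

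| Baseline mean | Power, flag | Power, count |
|---|---|---|
| 2.4 | about 58% | about 89% |
| 3.6 | about 44% | about 83% |

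**5. Ceiling or cut-off?** With a plain binomial baseline of mean 6.0, only 19% are at 8 or more, yet flag power is 53%, lower than the 69% found above with 31% at the ceiling. The demanding cut-off therefore causes much of the loss, and the ceiling adds to it.

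**The case against.** The strongest reply is that the protocol itself expects little prior knowledge. If 'minimal' means a baseline mean of about 2.4–3.6, few participants are at the ceiling, and with a large effect the flag loses almost nothing. The low-power rows require half or more of the patients to start well informed, which the protocol argues against. This stands as a limit on the size. It does not remove the point: 'minimal' is not a score, and at the same low baselines a smaller effect still costs the flag a good deal of power.

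The learning rates are also invented. Group C receives no oral health education, so 0.25 may be too high. At a baseline mean of 4.8, lowering it to 0.10, or raising Group A to 0.60, brings flag power above 99%. That too is fair, and it is why only a range can be given.

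Responder rules are a legitimate choice that this protocol uses widely, and nothing precludes an added analysis of the score. True, but for API and SBI mean comparisons are listed beside the percentages, and here none is.

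A reader might infer that the rule biases the comparison between arms. It does not: randomisation follows the baseline questionnaire, so the ceiling falls equally on the arms apart from chance. A reader might also infer that a large, well-informed part of the sample is affected. The documents do not show that such a part exists. Nor is this the only place where education is assessed: Process evaluation plans a self-assessment of educational value, although that is not a between-arm test of knowledge.

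**Conclusion.** The point holds as a loss of power and interpretability on one secondary outcome. The arithmetic is exact on the natural reading of the scale as a 0–12 count; that reading is an inference, because the questionnaire is not shown and the bullet also says Likert. Participants at 8–12 cannot be classed as improved, which is not the same as being unable to learn, and gains of up to 4 are ignored at every baseline.

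How much power is lost cannot be determined from the protocol. Across the assumed models it runs from negligible (low baseline, large effect) to severe (high baseline, or a modest effect even at a low baseline). The primary outcome and the total of 165 are unaffected. The change is worth making because it is cheap, not because the outcome has been shown to fail.

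**What to change.** Define the outcome as the 0–12 count at 6 weeks and at 12 weeks. Compare it between arms in a model with the baseline count as covariate, and report the mean difference with its 95% CI. Keep the rise of at least 5 as descriptive only, reported among participants with a baseline of 7 or less, and state that denominator. Reconcile the Likert label with the counting of 'yes' answers, so that the item format and the 0–12 scoring are unambiguous.

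The cost is rewording one secondary outcome, one extra model, and the loss of the simple percent-improved headline. The answers are already collected at all three visits, so no new data or participants are needed.

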**Methods**

Study Design

A dual-center, single-blind (examiner), parallel design randomised control trial of 165 patients attending an outpatient cardiac rehabilitation center within two public hospitals in Sydney, Australia. See **Figure 1.** for study flow diagram. The intervention populations will receive either a tablet-delivered specifically selected series of advertisement free, web-based educational videos covering multiple CVD and oral health related topics alone or partnered with individually tailored OHI. The control population will receive usual care as detailed below. The examiner will be blinded to the group allocation.

Patient population

The study population will be patients presenting to the outpatient cardiology rehabilitation centre participating in the Cardiac Education and Assessment Program (CEAP) at Westmead and Blacktown public hospitals, Sydney Australia. CEAP provides personalised support, exercise and education to help strengthen patient’s hearts after having a cardiovascular event and helps to lower risk of a future cardiovascular event (82). These patients attend due to a range of heart conditions such as coronary heart disease, heart failure, and those waiting for, or who have had a heart transplant. Due to the variety of heart conditions and co-morbidities, patients are placed on either a 6-week or 12-week program and can attend once or twice weekly. As these patients have taken part in this program, prioritising their cardiovascular health, and showing a motivation to reduce future risk of a cardiovascular event, we predict these patients will be interested in receiving education regarding oral health impacts on CVD.

Participant eligibility

A total of 165 participants will be recruited at either Westmead or Blacktown outpatient cardiac rehabilitation clinics who are attending as part of the CEAP program. Patients 18 years or older with a recent diagnosis of CVD , recent myocardial infarction and/or recent hospitalisation resulting from CVD will be approached for screening. This will include a clinical examination consisting of periodontal screening and recording (PSR), API, and sulcus bleeding index (SBI) (83) will be completed, followed by a self-report questionnaire. Patients will be excluded if:

- they have been diagnosed with heart failure.
- have/are waiting for a heart transplant,
- are too physically or mentally unwell on the day.
- have a cognitive impairment.

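### The confidence and motivation-to-improve outcomes name a state but are defined as a switch from baseline, so the reported percentages will not be the percentages confident or motivated; the knowledge rule has a ceiling at 8 of 12

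*Protocol*

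**What the plan says.** The rules are in the Protocol, Study outcomes, Secondary outcomes.

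- Confidence, on a 5-point Likert item: "A change in response from neutral, disagree or strongly disagree to agree or strongly agree compared to baseline will be considered confident".
- Motivation to improve oral health, on a yes/no item: "Answer change from no to yes will be considered motivated to improve their oral health".
- Motivation to attend an oral health practitioner (OHP), in the same bullet: either of two yes answers at follow-up "will be considered motivated to visit an OHP regularly". No baseline answer enters this rule.
- Knowledge of the link between heart and oral health: "A yes response increase of ≥ 5 out of 12 will be considered as an improved understanding".

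Table 1 (Data collection and management) has a row for "Motivation and confidence and to improve oral hygiene practices" and another for perceptions and knowledge. Both are marked at baseline, 6 weeks and 12 weeks. The protocol states no denominator for these outcomes. It does not say how a participant who is already favourable at baseline is classified. The Statistical analysis section names PSR, SBI and API as the baseline outcome measures that enter the model; baseline confidence, motivation and knowledge are not named.

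**The concern.** A reader of the results will take a percentage confident or motivated to mean the share of participants who are so at follow-up. The two rules produce something else: the share who moved from an unfavourable to a favourable answer. Someone who agrees at both visits does not meet the rule. Neither does someone who agreed at baseline and no longer does, so a maintained good answer and a lost one are treated alike. Because only upward moves count, ordinary response fluctuation adds successes in every arm with nothing set against them.

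The motivation bullet also uses one word for two quantities, a change for improving oral health and a follow-up status for attending an OHP. The two percentages cannot be read side by side.

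For knowledge, the label does say improvement, so a change rule fits it. The weakness there is a fixed ceiling, and a 13-point scale is reduced to yes or no.

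Gains in awareness, motivation and confidence are among the hypotheses stated at the end of the Introduction, so these outcomes carry part of the trial's message.

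**Working it through.** **1. Who can meet each rule**

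| Outcome | Baseline answers that can qualify | Baseline answers that cannot |
|---|---|---|
| Confidence | 3 of 5 levels (strongly disagree, disagree, neutral) | 2 of 5 levels (agree, strongly agree) |
| Motivation to improve | no | yes |
| Motivation to attend an OHP | all | none |
| Knowledge | 0 to 7 | 8 to 12, since 12 − 5 = 7 |

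The knowledge bullet mentions a Likert scale but counts yes responses out of 12. I take it as a 0–12 count.

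**2. What is reported against what is true**

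Let q be the share favourable at baseline, c the conversion rate among the rest, and l the loss rate among those favourable at baseline.

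- Rule, all participants in the denominator: (1 − q)c
- Rule, only baseline-unfavourable participants in the denominator: c
- Favourable at follow-up: q(1 − l) + (1 − q)c

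With everyone in the denominator, the reported figure falls short of the true one by q(1 − l) in each arm. With the restricted denominator it is a conversion rate. In general, neither is the percentage confident.

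The protocol gives none of q, c or l. The table assumes l = 0. The 80%/40% conversion rates are hypothetical; 40%/15% are borrowed from the API rates in the Sample size section. Entries are Group A / Group C.

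| q | c | Rule, all | Rule, baseline-unfavourable only | Favourable at follow-up | Difference, rule (all) | Difference, status |
|---|---|---|---|---|---|---|
| 50% | 80/40 | 40/20 | 80/40 | 90/70 | 20 | 20 |
| 70% | 80/40 | 24/12 | 80/40 | 94/82 | 12 | 12 |
| 20% | 40/15 | 32/12 | 40/15 | 52/32 | 20 | 20 |
| 40% | 40/15 | 24/9 | 40/15 | 64/49 | 15 | 15 |
| 60% | 40/15 | 16/6 | 40/15 | 76/66 | 10 | 10 |
| 80% | 40/15 | 8/3 | 40/15 | 88/83 | 5 | 5 |

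For q = 70%: 0.3 × 0.80 = 0.24 and 0.3 × 0.40 = 0.12; adding 0.70 gives 0.94 and 0.82.

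**3. The contrast between groups**

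Under the rule with all participants the difference is (1 − q)(c_A − c_C). For follow-up status it is (1 − q)(c_A − c_C) − q(l_A − l_C). The two are equal unless losses differ between arms, as the last two columns show. The fault lies in the label and in the missing losses, not in the absolute difference.

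**4. Why the fix needs baseline adjustment**

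The protocol gives no sample size for these outcomes. Its total of 165 does reproduce for the primary outcome. With 40% against 15%, two-sided 5% and 80% power, n = [1.960√(2 × 0.275 × 0.725) + 0.842√(0.40 × 0.60 + 0.15 × 0.85)]² / 0.25² = 48.9, so 49 per arm; 49/0.9 = 54.4, so 55; 3 × 55 = 165.

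With 49 evaluable per arm and conversion of 40% against 15%, power at q = 20, 40, 60 and 80% is:

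- rule, all participants: 67, 52, 35 and 19%
- baseline-unfavourable participants only: 71, 58, 42 and 23%
- follow-up status without adjustment: 52, 32, 19 and 10%

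Unadjusted status would be the weakest test. When l = 0, a test stratified by baseline status draws all its information from the baseline-unfavourable stratum, so it has about the power in the second line.

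**The case against.** The strongest reply is that these are late-listed secondary items, that randomisation balances baseline status in expectation, and that a change rule is a legitimate way to show an educational effect. All of that is true. It limits the consequence but does not repair a label that says confident or motivated.

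Several stronger readings are tempting, and the documents do not support them.

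- **That already-favourable participants are scored as failures.** No denominator is stated. They may be left out, and a statistical analysis plan may settle this. What holds under any denominator is that they cannot be counted as confident or motivated.
- **That the rule dilutes the absolute difference.** It does not: 12 and 20 points either way in the first two illustrations.
- **That the ceiling is sure to bind.** The Patient population text speaks of participants "showing a motivation to reduce future risk of a cardiovascular event", which concerns cardiovascular risk, not the oral health items. The Conclusion calls oral health knowledge in this population minimal, so the knowledge ceiling may seldom be reached.
- **That the habits outcome shares the fault.** It reads "Improved oral hygiene habits as reported by an increase in brushing frequency and/or inclusion of interproximal cleaning, comparing baseline to follow-up". Someone already cleaning between the teeth can still qualify by brushing more often, and the reverse. It is also named as an improvement.
- **That OHP-visit motivation requires a low start.** It uses the follow-up answer alone.
- **That SBI has the reverse fault.** "Assess the percentage in each Group that has reached clinically significant SBI scores of ≤25"% is a follow-up status, which is the form recommended below for confidence and motivation, and baseline SBI is already to be in the model.

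**Conclusion.** The point holds for two outcomes, confidence and motivation to improve. Each names a state and is defined by a one-way transition, so the reported percentage will not be the percentage confident or motivated, and losses will go unseen. This follows from the wording alone and needs no assumption. For knowledge the point is narrower: a baseline of 8 or more cannot succeed, and the cut-off discards information.

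The size cannot be computed from the protocol. With all participants in the denominator and no losses, the reported figure is too low by exactly the share already favourable at baseline, that is 20 to 80 percentage points over the assumed range. A reader might infer bias between the arms, but randomisation gives no ground for that. The primary API outcome is untouched. This should be corrected before analysis, as a matter of secondary outcomes.

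**What to change.** - **Confidence and motivation to improve.** Define each as status at follow-up (agree or strongly agree; yes), at 6 and at 12 weeks. Compare groups with adjustment for baseline status, for example by stratifying on it. Status would then have the same meaning in both halves of the motivation bullet, and losses would count.
- **Conversion.** Report it as a supporting result, under that name, only among participants not favourable at baseline, with that denominator shown.
- **Knowledge.** Analyse the 0–12 score by ANCOVA on the baseline score at each visit. Keep the gain of at least 5 as a descriptive summary.

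The cost is a rewording of these bullets in the protocol, matching text in the statistical analysis plan, and a small amount of extra analysis. Table 1 shows that the items are already collected at all three visits, so no new data are needed.

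### The confidence and motivation outcomes are labelled as states but scored only on a switch to a positive answer, so read literally they leave out participants positive throughout and merge losses with never-positives

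*Protocol*

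**What the plan says.** In the protocol, the secondary outcomes under Study outcomes include confidence to improve oral hygiene habits, on a 5-point Likert item, with this rule: "A change in response from neutral, disagree or strongly disagree to agree or strongly agree compared to baseline will be considered confident". The next bullet covers motivation and has two parts. For improving oral health the rule is "Answer change from no to yes will be considered motivated to improve their oral health". For seeing an OHP it is different: either of two affirmative responses at follow-up "will be considered motivated to visit an OHP regularly", and no change from baseline is required.

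No denominator is stated for either switch rule. The Statistical analysis section states the intention-to-treat principle for API only, so it does not settle the matter. Table 1 (Data collection and management) lists "Motivation and confidence and to improve oral hygiene practices" at baseline, 6 weeks and 12 weeks.

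The Patient population section describes those attending as "showing a motivation to reduce future risk of a cardiovascular event" and adds that "we predict these patients will be interested in receiving education regarding oral health impacts on CVD". No baseline rate of confidence or motivation is given anywhere.

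**The concern.** The two rules measure a change but name it as a state. A reader who sees that x% of an arm were confident will take it as the share who are confident, when it is the share who became so. Participants already positive at baseline cannot meet the rule, whatever happens to them afterwards. If they stay in the denominator they lower the percentage, and any of them who deteriorate leave no trace in the outcome.

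The Introduction hypothesises that the programme will motivate patients and give them confidence, so these outcomes bear on a stated hypothesis. What is at stake is the meaning of two reported percentages and whether harm to confidence or motivation could appear in the defined outcome.

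**Working it through.** **1. The rule, pattern by pattern** (positive = agree or strongly agree, or yes)

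| Baseline | Follow-up | Meets the rule? |
|---|---|---|
| not positive | positive | yes |
| positive | positive | no |
| positive | not positive | no |
| not positive | not positive | no |

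The last three patterns are indistinguishable in the derived outcome. With q the share positive at baseline, the percentage meeting the rule over all participants is (1 − q) × conversion, so it can never exceed 1 − q. This step needs no assumed rates.

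**2. The plan's own figure.** The protocol gives no calculation for these outcomes. Its sample size, with 40% and 15% read as proportions, two-sided 5% error and 80% power, gives 49 per arm by the pooled two-proportion formula without continuity correction. Then 49/(1 − 0.10) = 54.4, rounded up to 55, and 3 × 55 = 165, as stated. The point here does not alter that figure; 49 per arm is used below as the evaluable number.

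**3. Illustration.** Assumptions, none of them from the protocol: q = 30%, 50% or 70%; conversion among those not positive at baseline is 60% in Group A and 30% in Group C.

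Power = Φ{[d√n − 1.96√(2p̄(1 − p̄))] / √(pA(1 − pA) + pC(1 − pC))}, where d = pA − pC and p̄ is the mean of the two proportions.

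At q = 30%, all participants (n = 49): pA = 0.70 × 0.60 = 0.42; pC = 0.70 × 0.30 = 0.21; d√n = 0.21 × 7 = 1.470; 1.96 × √0.43155 = 1.288; denominator √0.4095 = 0.640; power = Φ(0.285) = 61%.

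At q = 30%, restricted to those able to convert (n = 49 × 0.70 = 34.3): 0.60 vs 0.30; d√n = 1.757; 1.96 × √0.495 = 1.379; denominator √0.45 = 0.671; power = Φ(0.564) = 71%.

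| q | Ceiling | Rule, A vs C | Gap | Power, rule | n per arm able to convert | Power, restricted |
|---|---|---|---|---|---|---|
| 30% | 70% | 42 vs 21% | 21 | 61% | 34.3 | 71% |
| 50% | 50% | 30 vs 15% | 15 | 43% | 24.5 | 56% |
| 70% | 30% | 18 vs 9% | 9 | 25% | 14.7 | 37% |

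The restricted gap stays at 30 points throughout.

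**4. Participants positive at both visits.** If 95% of those positive at baseline stay positive, q × 0.95 = 28.5%, 47.5% or 66.5% of an arm is positive at both visits and not counted.

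**5. Deterioration.** The share positive at follow-up is q × retention + (1 − q) × conversion. Suppose retention were 70% in A and 95% in C. The A − C difference in follow-up status would be (1 − q) × 30 − q × 25 points = +13.5, +2.5 or −8.5. The switch rule would still report +21, +15 or +9, because retention does not enter it.

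**6. Power of follow-up status against the rule.** With 95% retention in both arms, the status gap is again (1 − q) × 30 = 21, 15 or 9 points. Unadjusted power at 49 per arm is 57%, 37% or 20%, slightly below the rule's 61%, 43% or 25%.

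**The case against.** The Introduction says the study will assess changes in motivation and confidence. A switch-to-positive outcome serves that aim, and the neighbouring outcomes on habits and understanding are also improvement measures. Under randomisation the rule does not favour either arm when there is no effect. The denominator is unstated rather than wrongly stated, and a statistical analysis plan could restrict it to those not positive at baseline. Participants positive throughout would then be set aside rather than counted against their arm.

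Much of this stands. Scoring stable positives as failures is the literal reading, not an established intention. But a restricted denominator would still leave losses out of the outcome, and the label would still name a state. The OHP-visit rule in the same bullet is judged on the response alone, which shows that the protocol can define a state when it means one.

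A reader might infer three stronger things that the documents do not support:

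- **Follow-up status has more power than the switch rule.** With equal retention the gap is the same and unadjusted power is slightly lower. An advantage appears only if retention is assumed to be better in Group A, for which the protocol gives no basis.
- **Most participants will start positive.** The Patient population text concerns cardiovascular risk and interest in education, not confidence in oral hygiene. The API entry criterion selects people with poor plaque control, and the Conclusion calls oral health knowledge in this population minimal. The baseline share is unknown.
- **Loss of confidence cannot be detected at all.** Table 1 has the answers collected at all three visits. Loss is hidden in the derived outcome, not in the data.

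**Conclusion.** The point holds for two secondary outcomes: confidence, and motivation to improve oral health. As written, each percentage is mislabelled, is capped at 1 minus the share positive at baseline, and gives losses the same code as never-positives. These conclusions follow from the wording alone; the cap and the omission of stable positives also assume that all participants are in the denominator, since no restriction is stated.

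The size depends on a baseline share that the protocol does not give. Over an assumed 30% to 70%, with assumed conversion of 60% vs 30%, a 30-point conversion gap appears as 21 down to 9 points. The supported gains from a change are a correct label, visible deterioration, and an undiluted conversion rate in the restricted analysis (illustratively 71% against 61% power at a 30% baseline share). The OHP-visit item, the primary outcome and the sample size of 165 are not affected. This is worth correcting but does not threaten the trial's main conclusion.

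**What to change.** Reword the two outcomes. Define confidence as agree or strongly agree, and motivation to improve oral health as yes, at the 6-week and 12-week visits. Compare arms with the baseline response as covariate: a logistic model for the yes/no item, and a logistic model (or a proportional-odds model on the full scale) for the 5-point item. Show the baseline-by-follow-up shift table by arm, so that stable positives and losses can be seen.

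If the switch is kept because change is of interest, report it only among participants not positive at baseline, state that denominator, and label it *became confident* or *became motivated*.

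The cost is rewording two secondary outcomes and a small amount of extra analysis. No new data are needed, because Table 1 already schedules these items at all three visits.
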